### Evaluation of the Process Outcomes

Process outcomes will be evaluated through comparison of aggregated anonymized data at the level of the participating general practices, by examining, for example, reconsultation rates for MSK pain over 6 months and referral rates to other services between practices in the stratified care versus usual care arms. In intervention practices, we will also investigate the proportions of patients for whom the electronic template is completed, and matched clinical management options are selected overall and by risk subgroup.

A descriptive analysis will be undertaken of physiotherapist data by the intervention arm (eg, waiting times, number of treatment sessions, and clinical grade of treating physiotherapist).

### Examination of Bias

Selection bias will be examined through scrutiny of the comparability of recruitment rates per trial arm and comparability in general practice and participant characteristics. Further, a comparison will be performed examining the characteristics of patients in which the electronic template is activated but who did not take part in the data collection (nonparticipants) with those who did participate in terms of practice distribution; pain intensity scores; location of MSK pain; and (within the intervention arm) the proportion of patients at low, medium, and high risk of persistent disabling pain (from the practice consultation IT template). Both crude descriptive and inferential statistics will be reported.

Differential attrition between trial arms will be examined and reported descriptively: frequencies for responses by trial arm will be recorded in the descriptive tables. We will compare baseline sociodemographic and clinical variables and (for response ≥1) monthly NRS pain intensity scores across level of completion of NRS pain intensity (level of completion is 0 to 6, where 0 is nonresponse, 1 responded once, and 6 responded to all 6 monthly follow-ups) to ascertain whether pattern of missingness is likely to be *missing completely at random*, *missing at random,* or *not missing at random*. If the overall follow-up rate of the primary outcome is over 5% different between trial arms and the pattern of missing data is *missing at random*, then we will undertake a multiple imputation (MI; via chained equations) analysis inclusive of baseline variables that are observed to be statistically associated with follow-up response. Further, if the pattern of missingness is seen to suggest that it is nonignorable, the MI sensitivity analysis will address missing data imputations with an incremented or reduced value corresponding to the overall baseline SD (thereby mimicking the nonignorable pattern).

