### Sample Size

In an average-sized UK general practice (6000 registered adults), we expect that about 800 potentially eligible patients will consult with the MSK pain sites of interest per year or 400 over 6 months. The feasibility and pilot trial showed that, on average, the template was activated 375 times over 6 months in each practice, and clinicians fully completed it in 41.1% (154/375) of cases (6 times per week), leading to a letter inviting the patient to participate in the data collection. From this, we expect that 40% of patients invited will return their initial questionnaire in the main trial, be eligible, and consent to further data collection (or 62 over 6 months in 1 practice). However, to be more cautious, given the general uncertainty in data and in generalizability of pilot estimates, we have conservatively estimated the average number of participants recruited per practice within 6 months in the main trial to be around 33% of those invited (or n=50 in 6 months or n=9 per month per practice).

The trial is powered at 90% to test the hypothesis of the overall superiority of stratified primary care versus usual care based on an alpha of 5% (two-tailed) to detect a small *effect size* (standardized mean difference) of 0.2 [54] in the primary outcome (pain intensity). An effect size of 0.2 was considered to be appropriate based on information from the feasibility and pilot trial, in which the proportion of responders in the 3 risk subgroups was 32% at low risk, 55% medium risk, and 13% high risk. Our previous trial of stratified care for patients with low back pain (the Start Back trial) found an effect size of 0.3 and 0.4 in the primary outcome (back pain–related physical function) in patients at medium and high risk, respectively. Therefore, we have assumed these standardized differences in this new trial [19]. In addition, the minimal clinically important difference for the numerical rating scale (NRS) pain intensity scores in MSK pain has been reported to be 1 point [55], which equates to an effect size of about 0.4, relative to an expected SD of about 2.5 [54]. We expect that there would be little or no difference between stratified care and usual care for patients in the low-risk subgroup. Hence, by multiplying these effects by the expected proportion within each subgroup, the overall effect size of interest is 0.2 (equating to an absolute mean difference of approximately 0.5 in pain intensity on a 0-10 scale).

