The sample size calculation takes into account the clustering of individual participants by practice and likely participant dropout over a 6-month follow-up (inflationary effects on sample size requirement) as well as repeated measurements and adjustment for corresponding baseline pain intensity score (deflationary effects). We have allowed for an Intraclass correlation coefficient of 0.01 based on previous patient-level data from primary care trials [56] as well as expected variation in recruitment per practice using a guideline coefficient of variation of 0.65 [57], and together with an expected loss to follow-up across all time points of approximately 25%, these factors combine to give a sample size inflation factor of ×2.3 (based on an average cluster size of approximately 50 participants per practice in 6 months). The correlation of data within 6 repeated measurements and correlation of follow-up scores with baseline score are typically 0.7 and 0.5, respectively [58], which combine to give a sample size deflation factor of ×0.5. The product of inflation and deflation effects results in a magnification of 1.15 compared with a conventional, individual patient, single follow-up comparison, whereby the sample size requirement would be 525 per trial arm (or 1050 in total). The adjusted sample size target is, therefore, 600 patients per arm (1200 in total) from 24 general practices (12 per arm).

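### The missing-not-at-random sensitivity analysis depends on a diagnosis that observed data cannot give, and its one shift size cannot show where the conclusion would change

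*Protocol article*

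**What the plan says.** Main Analysis of Primary Outcomes in the protocol bases the primary result on a three-level mixed model of the six monthly pain scores, with missing data handled under MAR.

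Examination of Bias then compares baseline variables and observed monthly pain scores across level of completion (0 to 6 months answered). From this it judges which of the three mechanisms is likely: missing completely at random (MCAR), MAR or MNAR. Two analyses hang on that judgement:

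- Multiple imputation (MI) by chained equations is done when two conditions both hold. The first is "If the overall follow-up rate of the primary outcome is over 5% different between trial arms"; the second is that the pattern is judged to be MAR.
- For MNAR, the rule is conditional in the same way: "if the pattern of missingness is seen to suggest that it is nonignorable, the MI sensitivity analysis will address missing data imputations". The size of the adjustment is then fixed, each imputed score being replaced "with an incremented or reduced value corresponding to the overall baseline SD". One size of shift is named, in either direction.

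Sample Size gives the scale of the problem: "an expected loss to follow-up across all time points of approximately 25"%. It also gives the target effect, "equating to an absolute mean difference of approximately 0.5 in pain intensity on a 0-10 scale".

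**The concern.** MAR and MNAR differ only in how missingness relates to the scores that were not seen, given those that were. A table of observed variables by completion level can contradict MCAR. It cannot tell MAR from MNAR, and participants at level 0 contribute no monthly score at all. A rule that waits for the data to suggest MNAR therefore waits for evidence that these data cannot supply. If the table looks unremarkable, the MNAR analysis need not be run and the MAR assumption behind the primary estimate is not probed.

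The 5% rule for the MAR-based MI is a poor guide too. A difference in follow-up rates is observable, but it does not measure bias: equal losses in the two arms can be selective in different ways.

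If the MNAR analysis does run, one shift of a full baseline SD gives one point in each direction. A reader needs to know how far from MAR the data would have to be before the conclusion changed, and one large step does not show that.

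**Working it through.** **Inputs.** All are from Sample Size unless marked.
- Two-sided alpha 5%, power 90%, standardized effect 0.2, absolute target 0.5 points.
- SD: the protocol says of the 1-point minimal important difference, "which equates to an effect size of about 0.4, relative to an expected SD of about 2.5". No SD specific to baseline is given. Assumed 2.5, range 2.0 to 3.0.
- Missing share: 25%, read as the share of monthly scores missing. The split by arm is not given. Assumed 25/25, then gaps of 5, 10 and 15 percentage points.
- ICC 0.01, coefficient of variation 0.65, cluster size 50, correlations 0.7 and 0.5.

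**Step 1. Reproduce the plan's sample size**, to confirm the precision used in step 4.
- Unadjusted: 2 × ((1.96 + 1.2816)/0.2)² = 525.4 per arm (stated: 525).
- Inflation: [1 + ((0.65² + 1) × 50 − 1) × 0.01]/(1 − 0.25) = 1.701/0.75 = 2.27 (stated: 2.3).
- Deflation: (1 + 5 × 0.7)/6 − 0.5² = 0.50 (stated: 0.5).
- Adjusted: 525 × 1.15 = 604 per arm with the stated factors, or 526 × 2.268 × 0.50 = 597 unrounded (stated: 600). The figures reproduce.

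**Step 2. Effect of a 1-SD shift on the arm difference.** With SD s and missing shares p₁ and p₀:
- one arm shifted: s × p
- both arms shifted alike: s × (p₁ − p₀)
- arms shifted in opposite directions: s × (p₁ + p₀)

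| Shift of 1 SD (s = 2.5) | Movement in points | Share of 0.5 target |
|---|---|---|
| One arm, 25% missing | 2.5 × 0.25 = 0.625 | 125% |
| Both alike, equal loss | 2.5 × 0 = 0 | 0% |
| Both alike, 5-point gap | 2.5 × 0.05 = 0.125 | 25% |
| Both alike, 10-point gap | 2.5 × 0.10 = 0.25 | 50% |
| Both alike, 15-point gap | 2.5 × 0.15 = 0.375 | 75% |
| Opposite directions, 25% each | 2.5 × 0.50 = 1.25 | 250% |

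For SD 2.0 to 3.0 the one-arm figure is 2.0 × 0.25 = 0.50 to 3.0 × 0.25 = 0.75.

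**Step 3. Equal follow-up does not mean no bias.** As an illustration, suppose 25% are lost in each arm. In one arm the unseen scores average 1 point above their MAR prediction, and in the other 1 point below. The difference is then wrong by 0.25 × 1 + 0.25 × 1 = 0.5 points, the whole target, while the difference in follow-up rates is zero.

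**Step 4. Where the conclusion would change.**
- SE implied by 90% power at the target: 0.5/(1.96 + 1.2816) = 0.154.
- If 0.5 is observed, the room before significance is lost is 0.5 − 1.96 × 0.154 = 0.198.
- One-arm shift that uses it up: 0.198/0.25 = 0.79 points, which is 0.79/2.5 = 0.32 SD (0.40 SD at SD 2.0; 0.26 SD at SD 3.0).
- Under a common 1-SD shift, the gap in loss that uses it up: 0.198/2.5 = 0.079, about 8 percentage points.

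A one-arm shift of 1 SD is therefore about three times the shift at which significance goes (1/0.32 = 3.1). A result that fails at 1 SD could have failed anywhere between 0 and 1 SD.

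**The case against.** The strongest reply is that this concerns sensitivity analyses only. The primary model, estimand and test are untouched. The model already uses all six monthly scores with age, sex and baseline pain, and missingness is reduced by reminders, telephone collection and substitution from the 6-month questionnaire. All of this is true. It limits the severity but does not mend the trigger, since a loss of about 25% is still expected after those efforts.

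Several stronger readings are tempting, but the document does not support them:

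- A reader might infer that with similar follow-up in both arms no sensitivity analysis would run. The 5% condition stands in the sentence on MAR-based MI. The MNAR sentence follows separately and does not repeat it, so the MNAR analysis could run with equal follow-up.
- A reader might infer that the 1-SD shift must either cancel or overwhelm the effect. The intermediate rows of the table rule that out, and at SD 2.0 a one-arm shift equals the target rather than exceeding it.
- A reader might infer that the imputation model admits only significant predictors of response. The text says such variables are included; it does not exclude others.
- The article does not say which arm or arms are shifted. The detailed analysis plan, which is not shown, may say so, and this point does not rest on that gap.
- A reader might conclude that MAR-based MI must always be run. The mixed model is already valid under MAR, so MI under the same assumption adds mainly auxiliary variables and making it conditional costs little.

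The protocol's language is that of judgement rather than proof. That is fair, but the decision still turns on a judgement that the comparison cannot inform.

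**Conclusion.** The concern holds in two respects, both about rules that the protocol states. First, the only analysis that would probe departures from MAR is made conditional on a pattern that cannot distinguish MAR from MNAR, so the assumption behind the primary result may go untested. The 5% follow-up threshold for the other analysis is no guide to bias either. Second, the one stated shift size does not show how robust the conclusion is. It moves the difference by about 0.63 points (0.50 to 0.75) in one arm, by 0 in both arms with equal loss and by about 0.125 with a 5-point gap. The tipping point under planned precision lies near 0.3 SD in one arm.

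These figures assume a baseline SD of 2.5 (range 2.0 to 3.0), 25% of monthly scores missing in the shifted arm, a shift that works against the observed effect, an SE that the shift leaves unchanged, and no truncation of imputed scores at 0 or 10. The change should be made, but nothing here invalidates the primary analysis.

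**What to change.** Remove the data-based trigger and run the delta-adjusted MI whatever the observed pattern. Use a graded set of shifts, for example from 0 to 1 SD in steps and in both signs, applied to each arm separately and to both arms. Report the shift at which the conclusion changes. Fix the set before unblinding: the protocol keeps the trial statistician blind but reports analysis in progress, so if allocation is already known to the analyst the results should be labelled post hoc. Keep the completion-level comparison as description and as a guide to auxiliary variables, and do not read a follow-up difference below 5% as reassurance. The cost is extra programming and one supplementary table. No new data are needed and the primary analysis is unchanged.

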### Health Economics

The health economics analysis will determine the cost-effectiveness of stratified care in comparison with usual, nonstratified care over 6 months. A cost-consequence analysis will initially be reported, describing all the important results relating to costs and consequences. Subsequently, cost-utility analysis will be undertaken from an NHS/PSS perspective to determine the cost per additional QALY gained. A broader costing perspective will be considered in a secondary analysis, taking into account NHS/PSS costs, private MSK-related health care costs, and productivity costs associated with time off work.

### Costs

Resource use information will be obtained on primary care consultations (eg, general practitioners and practice nurses), secondary care consultations (eg, hospital consultants and physiotherapists), prescriptions, hospital-based procedures (eg, diagnostic tests, injections, and investigations), length of inpatient stay, and surgery. Patients will be asked to distinguish between UK NHS and private provision. Cost data will be collected via a participant questionnaire at 6 months. Unit costs will be obtained from standard sources and health care providers, including the British National Formulary, Unit Costs of Health and Social Care, and NHS Reference costs [64-66]. Given that MSK pain is associated with significant lost productivity, information will also be collected from participants on occupation status, time off work related to their MSK problem, and reduced work performance (presenteeism). This will enable the calculation of productivity costs, allowing analysis from a broader societal cost perspective. The average wage for each respondent will be identified using the UK Standard Occupational Classification coding and annual earnings data for each job type [67].

### Outcomes

The outcome of interest for the economic analysis is QALYs and will be generated from participant responses to the EQ-5D-5L questionnaire at baseline and at the 6-month follow-up. The crosswalk value set will be applied to patient responses to obtain utility scores, in line with current National Institute for Health and Care Excellence recommendations.

### Data Analysis

The cost-utility analysis will be carried out on an ITT basis, with the aim of estimating the difference in costs and QALYs between the stratified care and usual, nonstratified care arms. Missing EQ-5D-5L and cost data will be imputed using MI techniques [68] to ensure that all trial participants are included in the final analysis. For each participant, a QALY score over the 6-month follow-up period will be estimated using the area under the curve approach [69]. Imbalances in baseline utility (EQ-5D-5L) scores between the stratified care and usual nonstratified care arms will be controlled for using a regression approach [70].

The total health care costs over the study period will be calculated by multiplying the resource items used by the respective unit cost and summing over all items. Differences in mean costs and QALYs between the stratified care and usual nonstratified care arms will be estimated. The data for costs are likely to have a skewed distribution; therefore, a nonparametric comparison of means (eg, bootstrapping) will be undertaken to estimate 95% CIs around costs.

Due to the nature of the trial, methods are required to address clustering in both costs and outcomes and to recognize the correlation between individual- and cluster-level costs and outcomes. The methods currently suggested in the health economics literature are multilevel models (MLM) and the 2-stage nonparametric bootstrap, using the Stata 15 [Stata Corp] command TSB) [71]. For the base case scenario, MLM will be used to estimate differential costs, differential QALYs, and incremental net benefits. The analysis will also allow us to control for covariates. The robustness of the results will be explored using sensitivity analysis. This will explore uncertainties in the trial data itself as well as the methods employed to analyze the data. A cost-effectiveness acceptability curve will be constructed to assess the probability that stratified care is effective at different willingness-to-pay thresholds. To estimate productivity costs, self-reported days off work will be multiplied by the average wage rate. The analysis will use the human capital approach.

Planned sensitivity analysis will include (1) a complete case analysis as an alternative to using an imputed dataset; (2) a broader societal perspective; and (3) additional exploratory analyses that will consider the cost-effectiveness of stratified care versus usual nonstratified care for patients in the low-, medium-, and high-risk subgroups separately. All analyses will be performed using StataCorp 15 software.

### Linked Qualitative Study

#### Theoretical Framework

Two theoretical frameworks will underpin the evaluation. First, the COM-B model [72] offers a way of understanding behavior in the context of complex interventions around 3 key determinants: *capability* (the psychological or physical ability to enact the behavior), *opportunity* (the physical and social environment that enables the behavior), and *motivation* (the reflective and automatic mechanisms that activate or inhibit behavior). Second, normalization process theory provides a framework for understanding how/why some new health care interventions are accepted and taken up, whereas others are less successful [73]. Both frameworks emphasize the broader sociopolitical contexts in which health behaviors and practices are situated and the importance of taking these contexts into account in understanding the adoption of new interventions [73,74].

#### Aim

This study aims to understand the ways in which stratified care is perceived and operationalized, from the perspectives of health care professionals and patients, taking into account individual, local, and national contexts.

#### Objectives

The specific objectives of our linked qualitative research will be as follows:

Identify the acceptability and impact on the consultation of using the clinician-completed version of the Keele Start MSK Tool and the extent to which the matched treatment options are viewed as being in line with clinical judgments on best practice.Understand the impact of stratified care on (1) individual clinicians; (2) general practice and physiotherapy services; (3) interprofessional and professional-patient communication; and (4) patients at low, medium, and high risk.Document any variation in experiences or views across different practices and services in the trial.

#### Methods for Linked Qualitative Study

An iterative, mixed methods approach will be adopted [50,75], with the quantitative data informing the qualitative data collection and analysis from both informing the overall findings and conclusions. Data will be drawn from clinicians and patients.

#### Clinicians

GPs and physiotherapists involved in delivering stratified care will be invited to participate in up to 3 separate focus groups held at approximately 4 GP practices. Where clinicians are unable to attend focus groups, arrangements will be made for individual interviews. Initial focus groups/interviews will explore clinicians’ views and experiences of delivering stratified care during the course of the trial. Follow-up focus groups/interviews will be conducted at a later stage once trial results are available to explore views on the trial results and, depending on these results, discuss potential implications for practice, policy, and service provision beyond the trial.

#### Patients

One-to-one semistructured interviews will be conducted to explore individual patient experiences. Patients at low risk will be interviewed approximately 2 months after their index primary care consultation, whereas patients at medium and high risk will be interviewed at approximately 4 months. This timescale will allow participants to reflect on their experiences of clinical management (including time to access any treatments), communication with the clinicians involved in their care, and their health care resource use over time.

### Sampling

Clinicians and patients will be sampled from the stratified care arm of the trial. GPs directly involved in the trial will be identified based on the diversity of practice characteristics, including size and geographic location. A sample of physiotherapists in linked participating services will also be invited to participate. Patients will be purposively sampled from baseline questionnaire responses to capture diverse characteristics, such as pain scores and health-related quality of life, risk subgroup, comorbidity, age, sex, and socioeconomic status.

